### Data collection and management

A paper Screening Form and a Data Collection Proforma (DCP) are used to capture trial data in real time. Patient identification on the DCP is through their unique trial number, allocated at the time of enrolment. The DCP becomes the paper source document; however, it is used in conjunction with the usual hospital practice for recording medical information.

On completion of ED trial processes, participant data are recorded via the InForm Electronic Data Capture system using an electronic Case Report Form (eCRF). These data are transcribed by the research nurse or a delegated data manager from the DCP onto the eCRF. To ensure accurate, complete and reliable data are collected, IQVIA™ (formerly QuintilesIMS™ Holdings, Inc.), the Contract Research Organisation for the MAGPIE trial, provides training to site staff in the form of investigator meetings, site initiation visits or teleconference training sessions. The data are validated, and discrepancy reports are generated following data entry to identify discrepancies, such as out of range values, inconsistencies or protocol deviations based on data validation checks programmed into the eCRF. A full electronic audit trail is created for data entry and any subsequent amendments. Prior to submission, each completed eCRF must be reviewed for accuracy by the Principal Investigator at the site, corrected as necessary and then approved. The Investigator’s e-signature serves to attest that the information contained on the eCRFs has been reviewed by the Investigator and is true and accurate. The monitor will review the eCRFs and evaluate them for completeness and consistency. The eCRF is compared with the source documents to ensure that there are no discrepancies between critical data.

The sites, the trial database and trial documentation are subject to quality assurance audit during the course of the trial by the sponsor or IQVIA™ on behalf of the sponsor. In addition, inspections may be conducted by regulatory bodies at their discretion.

### Statistical considerations

Statistical analyses are performed by IQVIA™ using SAS® version 9.4 or higher (SAS Institute, Cary, NC, USA). Any change to the data analysis methods will be mentioned in the statistical analysis plan. Any additional analysis, and the justification for making the change, will be described in the Clinical Trial Report.

#### Sample size estimation

The sample size calculations assume a treatment difference to placebo of 12.4 mm in adolescents (based on interim 15-min data from the MEOF-001 trial [16]) and 14 mm in younger children, leading to a combined overall difference to be detected of 13.3 mm. The expected variability is higher in younger children (standard deviation (SD) 28 mm) than in adolescents (SD 22.5 mm), resulting in a pooled SD of 27.1 mm.

A sample size of 110 evaluable patients per treatment arm provides at least 95% power to detect a treatment difference of 13.3 mm in change from baseline of VAS pain score after 15 min with a pooled SD of 27.1 mm. Approximately 220 patients will be randomised and treated, and the drop-out rate is expected to be minimal. This sample size will allow an overall power of the trial to deliver statistically significant results for the complete trial population.

The trial population will include a minimum of 88 children (40%) aged 6–8 years, 88 children (40%) aged 9–11 years and 44 adolescents (20%) aged 12–17 years. An exploratory subgroup analysis per age range will be conducted, but this is not expected to be sufficiently powered to demonstrate statistical significance.

#### Statistical analysis plan

The primary analysis shall be an intention-to-treat (ITT) analysis of the difference between methoxyflurane and placebo on the VAS, to include all patients who are randomised and receive trial treatment and undergo at least one post-baseline efficacy assessment. A pragmatic conversion of WBF-PRS scores to VAS scores (e.g. WBF-PRS 2 = VAS 20 mm, WBF-PRS 4 = VAS 40 mm, etc.) will be completed. The primary model will be an analysis of covariance (ANCOVA) of the VAS at 15 min following the start of inhalation of trial treatment with baseline pain as covariate, treatment and age group as fixed effect and site as random effect using the ITT population. The treatment effect shall be estimated as the average difference between the methoxyflurane-treated group and the placebo group at 15 min. Pain scores taken after the initiation of a rescue medication will be included in the primary analysis. This approach is conservative for the primary analysis and allows for patients with missing data at any time point to be included in the analysis with less bias than if patients are dropped from the analysis. Sensitivity analysis of primary endpoint pain values shall be performed using Worst Observation Carried Forward (WOCF). To exclude the possibility that conversion of any WBF-PRS scores (ordinal scale) into VAS scores (continuous scale) significantly influences the outcome of the trial, sensitivity analysis using a non-parametric test (Wilcoxon rank-sum test) will be performed.

Various methods will be used for secondary endpoint analyses. For treatment comparison of change from baseline for continuous variables with more than one measurement within a time period, repeated-measures analysis employing restricted maximum likelihood (REML)-based mixed-model repeated measures (MMRM) will be used. For continuous variables with baseline value and one post-baseline measurement, ANCOVA will be used, unless specified otherwise. Least square means (LSmeans), SE, LSmeans difference, 95% confidence interval (CI) and *p*-value will be presented. Logistic regression analyses adjusted for baseline will be performed for the binary variables, and the odds ratio and 95% CI for the odds ratio of treatment group comparisons will be given.

Analysis of safety will be for all randomised and treated patients, and according to the treatment actually received. Any protocol deviations will be defined and classified as major (i.e. affecting the primary endpoint) or minor before database lock and unblinding.

Demographic and baseline characteristics will be recorded prior to randomisation, and will be summarised by treatment group for all patients who are randomised and received trial treatment. Overall summaries will include descriptive statistics for continuous measures (number of observations, mean, SD, median, minimum and maximum) and for categorical measures (sample size and frequency).

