### Trial participants

#### Inclusion criteria

The following inclusion criteria apply:Age ≥ 6 years to ≤ 17 years.Attending an ED following minor trauma.Pain scores (at screening and just prior to administration of study treatment) measuring between 60 and 80 mm on the Visual Analogue Scale (VAS) [19] or, where the patient is unable to understand the VAS, pain scores between 6 and 8 using the Wong-Baker FACES® Pain Rating scale (WBF-PRS).

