### Primary outcome

The primary outcome is the change in VAS (including WBF-PRS scores subsequently converted to VAS values) at 15 min after the commencement of treatment.

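### The Wilcoxon test meant to rule out an effect of the Wong-Baker-to-VAS conversion has to use the converted scores, so it cannot rule that effect out

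*Protocol article*

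**What the plan says.** All references are to the protocol article.

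- **Primary outcome:** the endpoint is the "change in VAS (including WBF-PRS scores subsequently converted to VAS values) at 15 min after the commencement of treatment", so two instruments feed one variable.
- **Inclusion criteria:** Wong-Baker is the fallback instrument, used "where the patient is unable to understand the VAS, pain scores between 6 and 8 using the Wong-Baker FACES® Pain Rating scale". The expected share of such children is not given.
- **Statistical analysis plan, conversion:** "A pragmatic conversion of WBF-PRS scores to VAS scores (e.g. WBF-PRS 2 = VAS 20 mm, WBF-PRS 4 = VAS 40 mm, etc.) will be completed". This is multiplication by 10.
- **Statistical analysis plan, primary model:** an ANCOVA of the 15-minute VAS "with baseline pain as covariate, treatment and age group as fixed effect and site as random effect using the ITT population". No term for the instrument is listed.
- **Statistical analysis plan, sensitivity analysis:** the purpose is stated as "To exclude the possibility that conversion of any WBF-PRS scores (ordinal scale) into VAS scores (continuous scale) significantly influences the outcome of the trial", and the method is that a "sensitivity analysis using a non-parametric test (Wilcoxon rank-sum test) will be performed". No other analysis is tied to that purpose.

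**The concern.** The article links a named method to a named purpose, and the method cannot serve it. A rank-sum test is unaffected by a monotone transformation only when the transformation is applied to every score. The conversion is applied to the Wong-Baker scores alone. A different conversion would reorder Wong-Baker children against VAS children, and the test statistic would change with it.

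What the test does relax is normality and, in part, the assumption that the faces are evenly spaced. What it keeps is the assumption that a given face and its assigned number of millimetres mean the same amount of pain. That is the assumption a reader would most want tested.

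As normally understood, a rank-sum test also carries no baseline, age-group or site terms. If it disagreed with the ANCOVA, the disagreement could not be put down to the conversion. If it agreed, the report might say that a conversion effect had been excluded when it had not been examined.

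**Working it through.** **1. Inputs.** From the article: 110 per arm, difference 13.3 mm, pooled SD 27.1 mm (Sample size estimation); 1:1 allocation (Enrolment and randomisation); conversion ×10 (Statistical analysis plan). Assumed, because the article does not give them: two-sided alpha 0.05, Wong-Baker share 20-60%, the alternative mappings, the underlying pain distribution, and a smaller difference of 8 mm as a less favourable case.

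**2. The plan's own figure.** It states that "A sample size of 110 evaluable patients per treatment arm provides at least 95% power to detect a treatment difference of 13.3 mm".

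- SE = 27.1 × √(2/110) = 3.654 mm
- 13.3 / 3.654 = 3.640
- Power = Φ(3.640 − 1.960) = Φ(1.680) = 95.3% (noncentral t: 95.2%)

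The figure reproduces. The sample size is not at issue.

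**3. Why the pooled ranks depend on the conversion.** Under ×10, Wong-Baker 4 becomes 40 mm and ranks above a child at VAS 35 mm. If Wong-Baker 4 were instead equivalent to anything below 35 mm, the order would reverse. Within the Wong-Baker group, 2 < 4 < 6 holds under any increasing mapping. Only the comparisons across instruments are at risk, and the pooled test includes them.

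**4. How much this moves the result.** Simulated trials had 110 per arm, with 1,500 trials per setting. Entries are the share of trials in which the pooled Wilcoxon crosses p = 0.05 in either direction when ×10 is replaced.

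| Change to Wong-Baker scores | Variable | 13.3 mm | 8 mm |
|---|---|---|---|
| Three other monotone mappings, share 20-60% | 15-min score | 0.8-2.7% | 2.2-8.0% |
| Same three mappings | change from baseline | 0.6-2.7% | 2.1-4.9% |
| Constant shift of 10 or 20 mm, share 30-50% | 15-min score | about 2-6% | about 7-12% |
| Same shift | change from baseline | 0% | 0% |

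The last row is zero by algebra: (y + c) − (b + c) = y − b. Under the three mappings the p-value for the 15-minute score changed in 99-100% of trials, but usually by too little to cross 0.05.

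**5. Does agreement show anything?** In an extreme assumed case, 60% of children were on Wong-Baker, with a 22 mm effect in them and none in the VAS children. A t-test on converted scores, standing in for the ANCOVA, was significant in 92% of trials and the pooled Wilcoxon in 90%; the two agreed in 98%. A VAS-only Wilcoxon was significant in 4%. With no effect in either group, the rates were 4.9%, 5.0% and 4.7%, and the first two again agreed in 98%. The two analyses agree because they share the same numbers, so their agreement says nothing about whether the converted scores drive the result.

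**6. Check of the repair.** A van Elteren test of the 15-minute score, stratified by instrument, gave the same p-value under every monotone mapping. Its power at 13.3 mm was 93.8-94.3%, against 93.6-94.5% for the pooled test under ×10. In a further simulation both had 92-93%.

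The property is lost on change scores. Under ×10, a fall from 8 to 4 (80 − 40 = 40) ties with a fall from 6 to 2 (60 − 20 = 40). For a general mapping m they tie only if m(8) − m(6) = m(4) − m(2). With nonlinear mappings, van Elteren on change from baseline gave an altered p-value in 99-100% of trials and reversed significance in about 1-4%.

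**The case against.** The best defence is that the article frames the problem as one of measurement level, an ordinal scale treated as continuous. A rank test is a conventional answer to that, and it does deal with non-normality and part of the spacing problem. This stands: the test is not worthless. It does not support a claim to exclude an influence of the conversion.

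A second defence is that the article is condensed. It does not say in words that the test is pooled and unstratified, or which scores enter it, and a full analysis plan may say more. This stands as a caveat. But the article states both method and purpose, and a rank-sum test over both instruments has no other common scale to work on.

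Third, the numerical effect is small, and nil for a constant shift if change scores are ranked. This also stands, and it limits the weight of the point.

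Three stronger readings are tempting, and the documents do not support them:

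- **That the primary result is unsafe.** Allocation is randomised and instrument use should not depend on arm. In the no-effect simulation the error rate stayed near 5%.
- **That most of the sample is affected, because 80% are aged 6-11 (40% + 40%).** Wong-Baker is used only for children who cannot understand the VAS, and the article gives no share.
- **That the primary model must include an instrument term.** Nothing in the article shows the ANCOVA to be invalid without one; this would be a preference.

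**Conclusion.** The point holds, in a limited form. As described, the Wilcoxon test inherits the ×10 conversion and cannot exclude an effect of it. The fault lies in the sensitivity analysis and the claim attached to it, not in the validity of the randomised comparison or in the sample size.

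On the 15-minute score, other mappings reversed significance in roughly 1-6% of simulated trials at 13.3 mm and 2-12% at 8 mm. The upper ends come from a constant 10-20 mm mis-calibration, which disappears if change scores are ranked. These ranges rest on assumed Wong-Baker shares, mappings and pain distributions, so they indicate scale and do not predict this trial's result. The logical point needs none of these assumptions. It needs only that both instruments enter one test on converted scores, which is inferred from the Primary outcome and Statistical analysis plan sections. The change is worth making because it costs little and can be fixed before unblinding.

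**What to change.** For this sensitivity analysis, replace or supplement the pooled Wilcoxon with a van Elteren (stratified Wilcoxon) test of the **15-minute score**, stratified by instrument (VAS or Wong-Baker). Do not apply it to change from baseline, where invariance to the mapping is lost. Define the stratum by the instrument used before randomisation, and say how a child who switches instrument would be handled, because exact invariance assumes one instrument per child.

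Show the treatment effect separately by instrument as a descriptive display, labelled as low-powered. If the pooled Wilcoxon is kept, describe it as a check on distributional assumptions and drop the claim that it excludes a conversion effect.

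Cost: a wording change and slightly more analysis work, with no change in sample size and almost no loss of power. The instrument must already be known for the conversion to be applied, so no new measurement should be needed, although the article does not say that it is held as a separate data item. The rank test does not adjust directly for baseline pain; the ANCOVA still does.

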### Trial design

This is an international multi-centre, randomised, double-blind, placebo-controlled, explanatory phase III trial assessing the efficacy and safety of methoxyflurane delivered via the Penthrox® inhaler for the management of moderate to severe pain associated with minor trauma. Recruitment and randomisation are stratified by age group bandings of 6–8 years, 9–11 years and 12 to < 18 years in a 2:2:1 ratio. A trial flowchart is shown in Fig. 1.

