### Secondary outcomes—efficacy

Number and proportion of participants in each arm who achieve a 30% reduction in VAS score at 15 min.Number and proportion of participants in each arm who achieve a 30% reduction in VAS score at 5, 10 and 20 min.Change in pain intensity (VAS) at 5, 10, 15, 20 and 30 min, and every 30 min thereafter until the point of ED discharge.Number and proportion of participants in each arm requesting rescue medication within 20 min of start of treatment, and any time during treatment.Time to requesting rescue medication.Time to first-reported analgesic effect.Number of inhalations until first-reported analgesic effect.Whether the patient covered the dilutor hole in the inhaler during inhalation.Global medication performance assessment by patient, clinician and research nurse, using a 5-point Likert scale.

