### Enrolment and randomisation

Randomisation sequences, stratified by age group (6–8 years, 9–11 years and 12 to < 18 years in a 2:2:1 ratio), are prepared by an independent statistician. Patients are randomised in the ratio of 1:1 to the active (methoxyflurane) or placebo group. The IMP is packaged according to the randomisation sequence prepared by the independent statistician.

Following consent, an unblinded member of the trial team enrols the patient to the trial using the Interactive Web Response System (IWRS). At enrolment, the participant is allocated the next randomisation number in the appropriate stratum. Treatment allocation as per the randomisation scheme is maintained by allocating IMP or placebo with the next sequential patient number.

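### The logistic model for the binary secondary endpoints names baseline as its only adjustment and does not mention age group, the factor by which the trial randomises

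*Protocol article*

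**What the plan says.** Under Trial design the article states: "Recruitment and randomisation are stratified by age group bandings". The Enrolment and randomisation section repeats that the sequences are stratified in this way and gives the allocation within them: "Patients are randomised in the ratio of 1:1 to the active (methoxyflurane) or placebo group". Age group is the only stratification factor mentioned.

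Under Statistical analysis plan, the primary ANCOVA is specified "with baseline pain as covariate, treatment and age group as fixed effect and site as random effect". The next paragraph turns to the secondary endpoints. For continuous variables it names MMRM or ANCOVA without listing covariates. For binary variables it does state an adjustment: "Logistic regression analyses adjusted for baseline will be performed for the binary variables". It adds that odds ratios with 95% confidence intervals will be reported.

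The endpoints concerned are listed under Secondary outcomes—efficacy. The first is "Number and proportion of participants in each arm who achieve a 30% reduction in VAS score at 15 min", followed by the same proportion at 5, 10 and 20 minutes. A later item is "Number and proportion of participants in each arm requesting rescue medication within 20 min of start of treatment", and at any time during treatment.

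**The concern.** An analysis normally carries the factors by which patients were randomised. The primary model does so; the model stated for the binary endpoints names baseline and nothing else. The two adjustment sets stand in adjacent paragraphs and do not match.

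Two things follow if age predicts response and is left out of a logistic model. The treatment odds ratio moves towards 1, because an odds ratio that averages over a prognostic factor differs from one conditional on it. The usual standard error also ignores the balance that stratification created, so the test rejects slightly too rarely and some power is lost. The first-listed secondary efficacy outcome is among those affected. Leaving the choice open would also allow two models that give different odds ratios to be compared after unblinding.

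**Working it through.** **1. The article's own figure.** Sample size estimation gives 110 per arm, a difference of 13.3 mm, a pooled SD of 27.1 mm and power of at least 95%. Taking two-sided alpha 0.05 (an assumption; the article states none):

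power = Φ(13.3/27.1 × √(110/2) − 1.96) = Φ(0.491 × 7.416 − 1.96) = Φ(1.68) = 95.3%.

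The t distribution gives 95.2%, and 108 per arm would give 95%. The figure reproduces. It rests on the continuous primary endpoint, so nothing below touches it.

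**2. The cost of omitting age group.** The article gives no response rates, so this was simulated.

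- From the article: 220 patients; strata of 88, 88 and 44; 1:1 allocation within each stratum; baseline pain between 60 and 80 mm.
- Assumed: 35% placebo response at average covariates; treatment odds ratio 2.2 conditional on the covariates; baseline uniform over its range with a log-odds slope of −0.02 per mm; age effect linear in log-odds across the three bands, with an oldest-versus-youngest odds ratio of 1, 2, 4 or 8.
- Models fitted to the same simulated data: treatment + baseline, and treatment + baseline + age group. There were 3,000 runs per setting. The Monte Carlo standard error is about 0.4 points for type I error and 0.7 to 0.8 points for power.

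| Age odds ratio | Type I error, without / with age | Power, without / with age | Estimated OR, without / with age |
|---|---|---|---|
| 1 | 5.1% / 5.2% | 82.6% / 82.9% | 2.23 / 2.24 |
| 2 | 4.6% / 4.9% | 81.5% / 81.9% | 2.21 / 2.25 |
| 4 | 3.5% / 4.4% | 78.5% / 80.4% | 2.12 / 2.25 |
| 8 | 3.9% / 5.0% | 73.1% / 77.8% | 2.01 / 2.25 |

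Power lost by omission is 0.3, 0.4, 1.9 and 4.7 points. Type I error is never inflated. At age odds ratios of 4 and 8 the model without age group falls more than two standard errors below 5%, which is the conservatism described above. A second simulation (2,000 runs per setting, true log odds ratio 0.8, age effects of 1.0, 1.5 and 2.0 in log-odds) gave losses of 1.1, 2.8 and 3.7 points, in the same direction.

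**3. What age effect do the article's own figures imply?** It expects a treatment difference of 14 mm and SD 28 mm in younger children, against 12.4 mm and 22.5 mm in adolescents. Assume normal changes with mean μ and SD σ, the same placebo μ in both groups, and baseline b. The response probability is then Φ((−0.3b − μ)/σ).

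Example, placebo, b = 80, μ = 0:

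- younger: Φ(−24/28) = 0.196, log-odds −1.41;
- adolescents: Φ(−24/22.5) = 0.143, log-odds −1.79;
- difference 0.38, an odds ratio of e^0.38 ≈ 1.46.

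For b of 60, 70 and 80 and placebo μ from 0 to −25 mm, the difference runs from −0.10 to 0.38 on placebo and from −0.19 to 0.26 on active treatment. In simulations of that order (5,000 runs, adolescents differing by 0.3 or 0.5 in log-odds), power was 82.2% without and 82.6% with age group, and 82.3% and 82.8%.

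**The case against.** The strongest reply is that this is a condensed article. It does not say that baseline is the sole covariate, it lists no covariates for the secondary ANCOVA and MMRM, and it refers to a separate statistical analysis plan in which full model statements commonly sit. The shift of the odds ratio towards 1 is also not an error as such: the model without age group estimates a different but legitimate quantity. And the gain is negligible unless age is strongly prognostic, which the article does not show.

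Most of this stands. It settles the matter for the secondary ANCOVA and MMRM, where silence on covariates is no fault. It also rules out the inference that the plan itself expects age to predict response: the 12.4 versus 14 mm and 22.5 versus 28 mm figures describe treatment effects and variability, and under equal placebo means they imply only a small age effect on response. Age-specific placebo means are not given, so a larger effect is possible but not documented.

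The reply does not dispose of the binary models. There the article is not silent: it names an adjustment, and age group is not in it. Statistical considerations says that changes to the analysis methods are to be recorded in the statistical analysis plan, so the stated adjustment is the starting point.

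**Conclusion.** The point holds as a minor one. For the binary secondary endpoints the article names baseline as the only adjustment and does not mention the factor by which the trial randomises, while the primary model includes it. Run as written, the test is valid but slightly conservative, and the odds ratio is attenuated to the extent that age predicts response. The power loss is about 0 to 2 points for an oldest-versus-youngest odds ratio up to 4 and about 5 points at 8. These sizes rest on assumed response rates and age effects that the article does not give.

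Two stronger readings are not supported. A reader might infer that the plan deliberately excludes age group; the text does not say so, and the statistical analysis plan could already include it. A reader might also infer that the binary analyses would be invalid or give too many false positives; the simulations show no inflation of type I error. The primary analysis, the sample size and every stated figure are unaffected.

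**What to change.** Before unblinding, specify for the binary endpoints: *logistic regression with treatment, age group and baseline pain score*. If the statistical analysis plan already has this, confirming it is enough. The wording also makes clear that baseline means the baseline pain score for the rescue endpoints, which have no baseline value of their own.

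The cost is one line of text and two further model parameters. Age band is known for every randomised patient, so no data are lost, and in the simulation with no age effect the added terms cost no power (82.6% without, 82.9% with).
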